### Blinding

It will not be possible to blind the study participants or those delivering the interventions. The local research team reviewing hospital records and the trial statistician will also not be blind to the treatment allocation. The majority of outcome measures are patient-reported and collected electronically or via post, so clinicians involved in the care of patients will not be involved in outcome data collection within the trial. The research team member contacting the participants to offer support with remote hand strength measurements at 6 months after randomisation will be blinded to treatment allocation.

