#### Acceptability of the interventions

We will assess the acceptability of the interventions by therapist and participants’ adherence and their experiences with the WISE interventions.

Treating therapists’ adherence to the intervention protocol will be assessed by (1) number of therapy sessions provided by the therapists, (2) content of intervention sessions and (3) timing of sessions. For complete adherence, we expect one session to be provided and attended for the independent exercise group and three for the supervised exercise group. During each session, all core intervention components will need to be delivered. The first session will need to be delivered as soon as possible, at least within 3 weeks of cast/splint removal. Additionally, for supervised resistance exercise, all three sessions must be completed within 12 weeks from the first to last session.

In terms of participant adherence to exercise, we will record the proportion of participants who report performance of resistance exercises at home and use the exercise support materials (website and workbook).

As part of the feasibility evaluation, we will also conduct qualitative interviews with participants and a focus group with the treating therapists to understand their experience of the trial and trial interventions. Participant interviews will be undertaken via telephone/video call or face-to-face in order to understand the experience of (i) the intervention within the context of their daily life, (ii) what taking part in a randomised trial is like, and (iii) outcomes that are important to them. Up to 20 participants will be interviewed within 6 months of injury. Participants will be purposively sampled to ensure representation from each intervention group, including surgical and non-surgical management of their wrist. Patients who decline to take part in the randomised study will also be interviewed to explore the experience of (i) recovery from injury, thoughts and feelings about the intervention, what helped or hindered their recovery; (ii) thoughts and feelings about taking part in the trial and trial processes; and (iii) what they hope to achieve and challenges they have or may encounter.

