### Secondary exploratory outcomes

We will also collect the following exploratory outcomes as part of this feasibility study to determine their viability for inclusion in a future definitive trial.Wrist pain and function: Wrist pain and function measurement using the Patient Reported Wrist Evaluation (PRWE) [11] recommended by the Core Outcome Measures in Effectiveness Trials (COMET) guidance [12] for distal radius fractures will be followed. PRWE is a 15 item patient-reported questionnaire that assesses pain and functional difficulties in activities of daily living resulting from injuries affecting wrist joint area. The pain subscale has 5 items (each rated 0 = no pain to 10 = worst pain) and the function subscale has 10 items (each rated 0 = no difficulty to 10 = unable to do). Total score ranges from 0 to 100, higher scores indicate worse wrist pain and function.Upper extremity physical function: Patient Reported Outcome Measurement Information System (PROMIS) [13] Physical Function (Upper Extremity) questionnaires will be administered electronically. They are a Computer Adaptive Test, which are dynamic tests based on Item Response Theory. A mathematical model adapts the sequential questions asked based on a participants’ previous response. A tailored set of questions is therefore asked from a large item pool. PROMIS instruments are scored from 0 to 100 with 50 points representing the mean score for the US general population, higher scores indicate better function. This questionnaire has been found to be valid in the context of upper limb fractures in the UK [14, 15]. Participants with no Internet access will be able to complete a paper-based version of the questionnaire (PROMIS Upper Extremity Short Form, 7a).Self-efficacy: The Self-Efficacy for Exercise Scale [16] is a 9-item questionnaire (total scores range from 0 to 90, higher scores indicate higher self-efficacy for exercise) that will be used to assess participants’ confidence in their ability to do exercise.Exercise adherence: Participants will be asked to indicate how many times in the preceding week they have done specific exercises for their injured hand and upper extremity, to assess engagement with the advised exercises after wrist fracture.Quality of life: The EuroQol 5 Dimensions (EQ-5D-5L) is a validated, generalised and standardised instrument comprising a visual analogue scale (VAS) measuring self-rated health and a health status instrument, consisting of a five-level response (no problems, some problems, moderate problems, severe problems and unable) for five domains related to daily activities: (i) mobility, (ii) self-care, (iii) usual activities, (iv) pain and discomfort and (v) anxiety and depression [17]. Responses to the health status classification system are converted into an overall score using a published utility algorithm for the UK population. The EQ-5D health status scale ranges from negative scores − 0.594 [reflective of a patient’s quality of life being worse than death], 0 [death], to 1 [perfect health]. A respondent’s EQ-VAS gives self-rated health on a scale where the endpoints are labelled ‘best imaginable health state’ (100) and ‘worst imaginable health state’ (0).Health resource use: A bespoke health resource use questionnaire will be used to assess the number of primary and secondary care consultations, additional therapy appointments, further wrist x-rays and scans, surgery and over-the-counter pain medication prescribed, out-of-pocket expenses and work absence.Adverse events: Adverse events related to the randomised interventions will be recorded.

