
A serious AE (SAE) is any unexpected untoward medical occurrence relating to the trial interventions resulting in death, is life-threatening, requires inpatient hospitalisation or prolongation of existing hospitalisation or persistent or significant disability/incapacity. In the event of any SAE, the Clinical Trials Unit standard operating procedures will apply.

Foreseeable SAEs and adverse events not defined as serious that are related to the interventions will be recorded by participants or site staff but will not need to be reported immediately. These events will be recorded on patient-reported questionnaires or by the site investigators in the ‘Complications’ case report form if they become aware of such an event.

Foreseeable adverse events include:Increases in pain lasting more than 1 weekTreatment-related exacerbations of other medical conditions that do not meet the definition of serious (for example angina after exertion)Development of Complex Regional Pain SyndromeSurgery to the injured wrist (unless an adverse event directly related to the exercise intervention, in which case this would be an SAE)

Safety reporting will begin from the point of randomisation and end when the participant has reached their final main follow-up time point, at 6 months post-randomisation.Muscle strength of the upper limb: Force produced during cylindrical grip will be measured using a commercially available hand-held dynamometer in a sitting position, as recommended by the American Society for Hand Therapists [18, 19]. Three attempts will be recorded for each hand alternatively, starting from the uninjured side on two consecutive days. Participants are asked to wait a minimum of 30 s between recording measurements. The best grip score for each hand will be recorded.Balance and mobility: Participants will be asked Likert type questions on balance and mobility to assess how this is progressing since their injury.

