#### Three- and six-month follow-up

Participants will receive an electronic/paper invite to complete questionnaires which include the PRWE, PROMIS, EQ-5D-5L, self-efficacy to exercise, current balance and mobility status, exercise frequency, resource use and adverse events. Reminders will be sent by email, post and/or text message (according to the participant’s preference); if questionnaires are not completed, these will be followed by a phone call from the central team if required.

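### Site capture of adverse events is passive while therapy contact differs by arm, so detection is likely to be unequal; a uniform check in every arm would limit this

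*Protocol article*

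**What the plan says.** Under Secondary exploratory outcomes, the protocol article gives two routes for foreseeable serious events and non-serious events related to the interventions. The first is the participant: "These events will be recorded on patient-reported questionnaires". The second is the site, where investigators complete a Complications form "if they become aware of such an event".

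The section Three- and six-month follow-up describes the participant route. The questionnaire content includes "exercise frequency, resource use and adverse events", with no distinction by arm. Reminders go to those who do not respond, and "these will be followed by a phone call from the central team if required".

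Scheduled trial contact differs by arm. Usual care consists of advice at cast or splint removal. For the exercise arms, Acceptability of the interventions says "we expect one session to be provided and attended for the independent exercise group and three for the supervised exercise group".

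The Blinding section mentions a further source: "The local research team reviewing hospital records and the trial statistician will also not be blind to the treatment allocation". It does not say what that review is for. Health resource use is also asked of participants and covers "additional therapy appointments, further wrist x-rays and scans, surgery".

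Statistical methods plans no comparative testing. Outcome data are reported by randomised group if feasibility is not shown, and taken forward into the definitive trial if it is.

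**The concern.** A site can enter only what it learns, and its scheduled chances to learn follow allocation: 0, 1 or 3 therapy sessions beyond usual care. Two of the listed foreseeable events, a prolonged increase in pain and complex regional pain syndrome, are things a therapist could notice at a session. With the same true event rate, the supervised arm could then show more events simply because it is seen more often.

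The questionnaire offsets this only for those who return it. A participant who returns the 3-month form but not the 6-month form has only the site route for later events. A participant who returns neither has only the site route throughout.

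At stake is a safety table by arm if feasibility fails or, if it succeeds, data of unequal completeness entering a trial in which the arms are compared.

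**Working it through.** The document gives no adverse-event rate or detection rate, so it has no figure of its own to reproduce on this point. What follows shows the mechanism under stated assumptions.

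**Inputs from the protocol article**
- Trial therapy sessions *k* = 0, 1, 3 (Interventions; Acceptability of the interventions).
- Arm size: 4 per centre per month × 3 centres × 6 months = 72 (Sample size determination); 72/3 = 24 per arm at 1:1:1.
- Loss at 6 months: green below 20%, amber 20–30% (Table 1). 0.2 × 72 = 14.4 and 0.3 × 72 = 21.6 participants, or 4.8 to 7.2 per arm.

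**Assumed inputs**
- *r*, the proportion returning the questionnaire; *s*, its sensitivity for an event; *q*, the chance that one therapy session reveals the event; a true event rate of 20%.

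**Model.** Probability that an event is recorded = 1 − (1 − *rs*)(1 − *q*)^*k*.

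| r | s | q | Usual care | Independent | Supervised | Ratio, supervised to usual care |
|---|---|---|---|---|---|---|
| 1.0 | 1.0 | 0.1–0.5 | 100% | 100% | 100% | 1.00 |
| 1.0 | 0.9 | 0.1 | 90.0% | 91.0% | 92.7% | 1.03 |
| 1.0 | 0.9 | 0.5 | 90.0% | 95.0% | 98.8% | 1.10 |
| 0.8 | 0.9 | 0.1 | 72.0% | 74.8% | 79.6% | 1.11 |
| 0.8 | 0.9 | 0.3 | 72.0% | 80.4% | 90.4% | 1.26 |
| 0.8 | 0.9 | 0.5 | 72.0% | 86.0% | 96.5% | 1.34 |
| 0.7 | 0.7 | 0.1 | 49.0% | 54.1% | 62.8% | 1.28 |
| 0.7 | 0.7 | 0.5 | 49.0% | 74.5% | 93.6% | 1.91 |

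Example, fourth row: *rs* = 0.72; supervised = 1 − 0.28 × 0.9³ = 1 − 0.28 × 0.729 = 0.796; 0.796/0.72 = 1.11.

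**Non-responders alone** (*rs* = 0, therapy sessions the only source): 0%, 10% and 27% at *q* = 0.1; 0%, 50% and 88% at *q* = 0.5.

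**In events.** Expected true events per arm: 24 × 0.20 = 4.8. At *r* = 0.8 and *s* = 0.9, the excess recorded in the supervised arm is 4.8 × (0.796 − 0.72) = 0.4 at *q* = 0.1 and 4.8 × (0.965 − 0.72) = 1.2 at *q* = 0.5.

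**Other assumptions.** Now let *c* be overall site awareness in an arm, so capture = 1 − (1 − *rs*)(1 − *c*), with *r* = 0.8, *s* = 0.7 and *rs* = 0.56.
- *c* = 0 in usual care and 0.5 in supervised: 0.56 against 0.78, ratio 1.39. With 0.25 in supervised: 0.67, ratio 1.20.
- Some awareness in usual care, *c* = 0.20 against 0.35: 0.648 against 0.714, ratio 1.10.
- Both questionnaires able to report the event, same responders, independent reports: 0.8 × (1 − 0.3²) = 0.728 replaces 0.56. With *c* = 0 against 0.5: 0.728 against 0.864, ratio 1.19. With 0 against 0.25: 0.796, ratio 1.09.

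The session model lets every event meet all *k* sessions. An event arising after the first session meets fewer, and one arising after the last session meets none, so the model leans towards a larger imbalance.

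**The case against.** The strongest case against is that the main instrument does not depend on allocation. Every arm gets the same adverse-event question twice, with reminders and then a call. If that questionnaire is complete and sensitive, the imbalance disappears. This stands, and it is why the point is a risk and not an established bias.

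A reader might infer that events will certainly be found more often in the supervised arm. The documents give unequal opportunity, not detection rates, so they support no more than likely.

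A reader might also infer that events in people lost to follow-up are missed, or that sites learn nothing about usual-care participants. Neither is supported. Someone lost at 6 months may have reported at 3 months. Usual-care participants attend a fracture clinic, have treatment logs, can get telephone or video support, and can be referred locally for complications. Hospital staff may well learn of surgery or diagnosed complex regional pain syndrome in any arm. After the last therapy session, the passive route is weak in all arms alike.

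Three further points have weight. Only events related to the randomised interventions are recorded, so counts may differ by arm for reasons other than capture. No comparative test is planned, so little turns on this in the feasibility trial itself. The timing of the Complications form may be fixed in the full protocol or in the schedule figure, neither of which is shown.

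What remains is that the article does not merely omit a procedure. It states a capture rule, and that rule makes the site route conditional on awareness. Table 1 accepts up to 20% loss as green, so the plan does not count on a fully returned questionnaire.

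**Conclusion.** The point holds as a likely inequality of ascertainment of unknown size. Participant reporting is the same in all arms; site reporting is passive and has more scheduled opportunity in the supervised arm. For events after a participant's last returned questionnaire, it is the only stated route.

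Under the assumptions shown, the apparent ratio of supervised to usual care is 1.0 with a complete and sensitive questionnaire, about 1.1 to 1.4 in mid-range cases, and up to 1.9 at 70% response and 70% sensitivity. In an arm of 24, with a 20% event rate, 80% response and 90% sensitivity, that is about 0.4 to 1.2 extra recorded events. None of the response, sensitivity, detection or event rates comes from the document.

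The practical weight lies in what happens to the data: publication by group if feasibility fails, or transfer to the definitive trial if it succeeds. A change is worth making because it is cheap and the inequality, if present, is systematic.

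**What to change.** Replace the conditional wording with a fixed rule: the local research team completes the Complications form for every participant in every arm at the same time point, for example 6 months, with none as a permitted entry. Use the hospital-record review mentioned under Blinding, and state that it covers the listed events. Include questionnaire non-responders, within whatever consent remains. If the full protocol already does this, only the article's wording needs aligning.

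Add a source field to each event (questionnaire, record check, therapy session). Report events by arm and source, giving the number who returned each questionnaire as the denominator for that source. The arms can then be compared on the sources common to all. Surgery and additional therapy reported in the resource-use questionnaire offer a cross-check.

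Cost: about 72 record checks and one extra field. The site time is modest, though the present scope of the record review is not stated, so some of it may be new work. The reviewers are not blinded. Events that do not reach hospital records, such as prolonged pain, and events treated elsewhere will still be missed.

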### Sample size determination

In a definitive trial with two intervention groups and with the PRWE as primary outcome, a sample size of 486 participants would be needed, based on a standardised effect size of 0.33, power of 90%, an alpha error of 0.05 (2-sided) and inflating for 20% loss to follow-up. The effect size equates to a clinically meaningful difference of 6 points in the PRWE, and a standard deviation of 18 which is consistent with evidence from other cohorts [20–22]. Currently, we do not know whether it is feasible to conduct a definitive trial. To recruit 486 participants over 20 months in the definitive trial at six recruitment centres, we would need to recruit at least four participants per centre per month. In order to improve the precision of the estimate of the number of participants recruited per month we will recruit over a six month period. If we recruit on average four participants per centre per month we will recruit 72 participants at three feasibility study centres in a six month period.

### Data collection methods

#### Baseline data

Baseline sociodemographic, handedness, injury details will be collected. Participants will also complete the PRWE, PROMIS Upper Extremity, EQ-5D-5L, balance and mobility and Self-efficacy Exercise Scale.

#### Treatment logs

After the usual care or exercise (independent and supervised) sessions, the date, duration, session content, clinician profession and experience details, setting, mode of delivery and the material and resources issued will be recorded on treatment logs.

#### Three- and six-month follow-up

Participants will receive an electronic/paper invite to complete questionnaires which include the PRWE, PROMIS, EQ-5D-5L, self-efficacy to exercise, current balance and mobility status, exercise frequency, resource use and adverse events. Reminders will be sent by email, post and/or text message (according to the participant’s preference); if questionnaires are not completed, these will be followed by a phone call from the central team if required.

#### Six-month follow-up grip strength measurement

Only those participants who return the 6-month follow-up questionnaires will then immediately be sent a portable dynamometer and a grip recording form with written instructions on how to use the device and given access to a video guide. A member of the research team via telephone or video call will contact participants to offer the support to do the measurements if required. Participants will be provided with free-post return packaging to return the grip data and dynamometer.

#### Early discontinuation/withdrawal of participants

During the course of the trial, a participant may choose to withdraw early from the study at any time, without giving reasons, and without prejudicing their clinical care. Participants will not have the option to withdraw the data collected up until the point of withdrawal, as the data will be required for the intention-to-treat (ITT) main analysis and analysis of safety. The type of withdrawal and reason for withdrawal, if the participant is willing to provide one, will be recorded. In addition, therapists may discontinue a participant from the study treatment at any time if necessary to safeguard the safety or wellbeing of the participant, including but not limited to ineligibility (either arising during the study or retrospectively having been overlooked at screening). Withdrawn participants will not be replaced.

#### Data management

At enrolment, participants will be asked to indicate their preference for the delivery and completion of questionnaires—electronic or postal follow-up at 3 and 6 months. Data collected in electronic format will be entered directly onto the trial database, including the collection of documentary evidence of consent. All data entered will be encrypted in transit between the participants/recruitment centre and server. All electronic patient-identifiable information will be held on a server located in an access-controlled server room at the University of Oxford. The data will be entered into a Good Clinical Practice (GCP) compliant data collection system and stored in a database on the secure server, accessible only to the research team based on their role within the study. The database and server are backed-up to a secure location on a regular basis.

Identifiable data will be limited to contact details and will be accessed separately from the outcome data obtained from/about the participants and managed within the rules of the clinical database system. Direct access to source data/documents will be required for trial-related monitoring and/or audit by the Sponsor, NHS Trust or regulatory authorities. Contact details will be retained for 12 months after the last data collection. Electronic de-identified trial data will be retained for 3 years after publication of the trial findings. Site staff will have access to the centrally collected patient-reported outcome data for participants that they recruit at their site on Research Electronic Data Capture (REDCap), to ensure that they can download a complete dataset for their patients at the end of the trial.

### Statistical methods

Analysis methods will be guided by the demonstration of feasibility. If feasibility is not demonstrated and a definitive trial is not conducted, then outcome data for the ITT population will be analysed and reported for each randomised group. In this case the feasibility outcomes and baseline characteristics will be reported using descriptive statistics. Mean and standard deviation or median and interquartile range will be used for continuous variables and counts and percentages will be used for any binary or categorical variables. Missing data will be minimised by careful data management. No comparative statistical testing will be undertaken as this is a feasibility study and is not powered for this purpose.

If feasibility is demonstrated, outcome data will not be analysed by group as we would take participants and their data from the feasibility and pilot study forward into the definitive trial.

